### Outcomes

#### Primary outcome

Dressing failure: defined as requirement for initial IJ CVAD dressing to be replaced due to the dressing lifting at the edges at any point during CVAD dwell but prior to scheduled dressing change (scheduled dressing changes are every seven days). The requirement for dressing changes will be determined by clinical staff treating the patient, and the clinical indication for dressing change will be recorded. If a patient’s CVAD is removed prior to seven days with the primary dressing still in situ, the dressing will be considered not to have failed.

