#### Secondary outcomes

All-cause CVAD failure: a composite of failure resulting in CVAD removal. Includes pain, infiltration/extravasation, blockage/occlusion (with or without leakage), fracture, thrombosis, dislodgement (complete or partial), or haematomaIndividual types of CVAD failure resulting in CVAD removal [pain, infiltration/extravasation, blockage/occlusion (with or without leakage), fracture, thrombosis, or dislodgement (complete or partial)]‘Central line associated bloodstream infection’ defined as per the National Healthcare and Safety Network (NHSN) [20]‘Primary bloodstream infection’ defined as per the NHSN [20]‘Local infection’ as defined by the Centres for Disease Control and Prevention (CDC)/NHSN ‘Arterial or venous infection’ criteria [21]Loss of dressing integrity not requiring dressing change (i.e. lifting at edges with/without reinforcement required) assessed for all dressings per patientDressing dwell time (from dressing application to removal in days) assessed for all dressings per patientPremature dressing removal (before seven days from dressing application; all dressings per patient)Number of dressing changes (from first application to last removal; all dressings per patient)Device dwell-time (time from CVAD insertion to removal in hours)Serious adverse events (i.e. mortality, CLABSI, MARSI)Adverse skin events relating to MARSI (e.g. pain, itch, erythema, skin stripping, blister, skin tear, irritant contact dermatitis, maceration, folliculitis or infection) [22]Cost (cost and number of products used, cost of treating complications, staff time for device insertion), as informed by standard diagnosis related groups (DRGs), staff time estimates to apply and remove dressings and product costs.Staff and patient satisfaction on dressing application and removal (0 = not at all satisfied to 10 = completely satisfied) assessed at initial application, all dressing changes and final removal for all dressing changes per patient.Skin colonization, measured both descriptively (i.e. organism) and quantitatively (i.e. colony forming units)

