### Sample size

A total of 160 patients will be recruited. At 90% power and a significance level of 0.05, 77 patients per group are required to detect a 25% absolute difference in the primary outcome (control failure 50%, intervention failure 25% [2]). To account for potential attrition, three additional patients per group will be recruited.

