### Assignment of interventions: blinding

#### Who will be blinded

Due to the nature of the intervention, blinding of patients/clinicians and research staff to the intervention is not possible. However, the statistician will be blinded for analysis, and microbiology laboratory staff will be blinded when culturing swab growth. The infectious diseases consultant will also be blinded to treatment allocation when apportioning infection outcomes.

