Age Weight Height APACHE II Score Skin type • Very fair, fair, medium, olive, etc. Skin integrity • Good, fair, poor Date of hospital and ICU admission ICU admission type • Planned, emergent, IHT Primary reason for ICU admission • Medical, surgical, other Number of comorbidities Current infections • Blood, urinary, respiratory, etc. Current wounds • Yes, no	CVAD insertion site • Left or right IJ Placement of CVAD in IJ vein • High, mid, low Angle of CVAD lumens • Down, up, horizontal Number of CVAD lumens Place of CVAD insertion • ICU, OT, etc. Antimicrobial-impregnated CVAD • Yes, no Inserter type • ICU registrar, ICU consultant, anaesthetic registrar, etc. Number of insertion attempts Technologies used during insertion • Ultrasound, x-ray, ECG, etc. Hair clipped prior to CVAD insertion • Yes, no Dressing site • Neck, chest, other Diaphoretic at insertion site • Yes, no Facial hair at insertion site • Yes, no Dressing and securements in addition to ‘standard care’ • Sutures, bordered transparent dressing, tissue adhesive, etc. Date and time of first MLA application Staff/patient satisfaction with dressing application • 0 = not at all satisfied, 10 = completely satisfied	Date/time of check Reason why check not able to be completed • Patient not available, etc. Is randomised dressing still in situ • Yes, no Dressing site • Neck, chest, other Dressing and securements in situ • Sutures, bordered transparent dressing, tissue adhesive, etc. Condition of current dressing • Clean, dry, intact, lifting at edges, etc. How many edges of the dressing are lifting or requiring reinforcement Complications at CVAD insertion site • Redness, purulent discharge, pain, etc. Has the patient mobilised, been diaphoretic, restless/agitated • Yes, no Signs and symptoms of skin injury/reaction • Pain, itch, redness, rash, papules, stripping, blister, etc. Suspected cause of MARSI or skin injury/reaction Extent of redness, rash or maceration if applicable Positive bloodstream infections since last daily check • Yes, no Number of administration sets What is the CVAD currently being used for • Fluids, blood products, CVP monitoring, blood sampling, etc. Dressing changes since last daily check • Date/time, reason for dressing change, staff/patient satisfaction, etc.	Date/time of CVC removal Reason for CVC removal • Treatment complete with/without complications, patient deceased, routine replacement, etc. Complications at time of CVC removal • Occlusion, unable to aspirate, accidental removal, suspected infection, MARSI, etc. Signs and symptoms of skin injury/reaction • Pain, itch, redness, etc. Extent of redness, rash or maceration if applicable Pain, tenderness, redness, swelling at CVC insertion site Patient mobility at time of CVC removal • Independent, requires assistance, bed-bound, etc. IV antibiotics administered during CVC dwell • Yes, no Patient diagnosed with delirium • Yes, no Staff/patient satisfaction with dressing removal • 0 = not at all satisfied, 10 = completely satisfied	Was the patient alive at 48 h after CVC removal? • Yes, no Date/time of death SAEs Results of CVC tip culture Results of CVC insertion site swabs Results of blood cultures

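### The secondary outcome for loss of dressing integrity excludes lifting that led to a dressing change, so a lower rate has no fixed meaning and the comparison can point against the better-adhering arm

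*Protocol article*

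**What the plan says.** All references are to the protocol article.

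- Secondary outcomes lists "Loss of dressing integrity not requiring dressing change (i.e". The bracket goes on to describe lifting edges, with or without reinforcement, and the outcome covers every dressing a patient has.
- Primary outcome takes the other part of the lifting, for the first dressing only: "requirement for initial IJ CVAD dressing to be replaced due to the dressing lifting at the edges at any point during CVAD dwell", before the scheduled seven-day change.
- The same section says who draws the line between the two: "The requirement for dressing changes will be determined by clinical staff treating the patient". Who will be blinded adds that "blinding of patients/clinicians and research staff to the intervention is not possible".
- Statistical methods for outcomes sends the remaining secondary clinical outcomes to a between-group comparison by suitable parametric or non-parametric methods, with significance at P < 0.05. Nothing there combines this outcome with lifting that ended in a change.
- Table 1, daily check, records the condition of the dressing, "How many edges of the dressing are lifting or requiring reinforcement", and any dressing change since the last check with its reason.

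**The concern.** The outcome is a remainder: lifting dressings less those judged to need replacement. The part removed is determined after randomisation and is what MLA is meant to reduce. If MLA turns lifting that would have needed a change into lifting that does not, those dressings leave the replaced group and enter this outcome, raising its rate in the MLA arm although adhesion has improved. A different threshold for changing dressings in the two arms, which is possible when staff know the allocation, would move dressings in the same way with no difference in adhesion.

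At stake is the reading of one secondary comparison. A significant difference in either direction could not be interpreted alone. No listed outcome counts any lifting across all dressings: premature removal and number of changes cover all dressings but are not restricted to lifting.

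**Working it through.** **The plan's own figure.** Sample size gives "control failure 50%, intervention failure 25" per cent and states: "At 90% power and a significance level of 0.05, 77 patients per group are required". Two-sided, pooled variance, no continuity correction:

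n = [1.960 × √(2 × 0.375 × 0.625) + 1.282 × √(0.50 × 0.50 + 0.25 × 0.75)]² / 0.25² = (1.342 + 0.848)² / 0.0625 ≈ 76.7, so 77 per group.

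The figure reproduces. The point does not rest on it; only the two planning rates are borrowed below.

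**Identity.** For initial dressings, let L be the proportion with any lifting, R the proportion replaced because of lifting, and q = R/L the chance of a change given lifting. If replaced dressings are fully excluded, the outcome as defined is

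L − R = L × (1 − q).

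**Inputs.** R = 50% (control) and 25% (MLA), from Sample size. L is not given anywhere, so the values below are assumptions.

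| Any lifting, control v MLA | Outcome as defined (L − R) | q, control v MLA | Reading |
|---|---|---|---|
| 60% v 60% | 10% v 35% | 83% v 42% | apparent harm, though any lifting is equal and replacement is halved |
| 60% v 50% | 10% v 25% | 83% v 50% | reversed |
| 70% v 60% | 20% v 35% | 71% v 42% | reversed |
| 70% v 45% | 20% v 20% | 71% v 56% | 25-point benefit hidden |
| 70% v 35% | 20% v 10% | 71% v 71% | correct |

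Within this illustration the sign reverses when MLA cuts any lifting by less than 50 − 25 = 25 points. With q equal in the two arms, the outcome is proportional to L and the sign is right. For example, q = 70% gives L = 71% v 36% and an outcome of 21% v 11%.

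**If earlier lifting counts.** The article does not say how to treat a dressing that lifts at one check and is changed later. Suppose a fraction f of replaced dressings, the same in both arms, still counts for the earlier episode. The outcome is then L − (1 − f)R, and reversal needs (1 − f) × 25 points to exceed the difference in L. For 60% v 50% that is (1 − f) × 25 > 10, so f < 0.6. The exclusion weakens as f rises and disappears only at f = 1.

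**The case against.** The strongest case on the other side has four parts.

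1. **Units.** The 50% and 25% are rates per patient for the first dressing, while the outcome covers all dressings. At patient level the two categories are not exclusive: a patient whose first dressing was replaced may have a later one that lifts and is left in place. No per-dressing replacement rate is given. This stands, so the table shows direction and not expected size. For the same reason no power is attached to the apparent harm.
2. **Assumed inputs.** The reversing rows need q to be lower with MLA, and no passage documents such a shift. This also stands. A reader might infer that the outcome will reverse, or that the 25-point threshold is a property of the trial. The documents support neither: the rates of any lifting are assumptions, and a similar q in both arms gives the right sign.
3. **The rest is covered.** The primary outcome takes lifting that led to replacement of the first dressing, dwell time, premature removal and number of changes cover all dressings, and the label openly says that changed dressings are excluded. So a reader should not infer that the trial's aim is undermined. It remains true that the outcome would be compared between arms without a settled direction of benefit.
4. **Left to an analysis plan.** A summary of any lifting could be added there. But the definition is already stated in the article, and a choice of test would not repair it.

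**Conclusion.** The concern holds as a limit on interpretation. As defined, the outcome can favour the arm with more replacements, and it does so when MLA mainly makes lifting milder or when unblinded staff apply different thresholds by arm. It points the right way when the chance of a change given lifting is similar. Reversal is therefore possible and not certain, and its size cannot be estimated from the document.

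This rests on reading the exclusion as removing at least those dressings changed when lifting was first seen. One secondary outcome is affected. The primary outcome, the sample size and the main conclusion are not.

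**What to change.** Redefine the between-group outcome as any edge lifting or reinforcement recorded at a daily check, or given as the reason for a dressing change, whether or not the dressing was then replaced. An ordered outcome would also serve: intact, lifting without change, lifting with change. In the 60% v 50% illustration, leaving aside changes for other reasons, the categories read 40%, 10%, 50% in control and 50%, 25%, 25% with MLA, so the direction is plain. Keep lifting without a change as a descriptive breakdown only.

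The cost is one sentence in the outcome definition and no new data item, since Table 1 already collects what is needed. There are two downsides. The new outcome overlaps with the primary outcome for first dressings. Lifting at weekends that did not lead to a change may also be under-recorded, because there are no in-person weekend checks and the bedside log is described as covering the number of and reasons for changes. The present definition has that second weakness too.

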Traditional practice for dressing and securement of internal jugular (IJ) CVADs has been the use of polyurethane transparent dressings with or without additional securement from sutures or commercial sutureless stabilisation devices [9]. However, current dressing and securement practices are often inadequate, as IJ CVAD dressings frequently fail as a result of diaphoresis, beard growth, multi-vector pull forces related to the ‘drag’ of multiple infusion lines, intermittent ‘catching’ on objects and increasingly early mobilisation of ICU patients [2, 10, 11]. Each time a dressing fails it requires replacement, therefore placing patients at a higher risk of medical adhesive-related skin injury (MARSI) [12]. CVAD-related MARSI typically includes bruising, local site infections, pressure injuries, maceration, dermatitis, and mechanical injuries such as skin tears and blisters which have the potential to be disfiguring and lead to CVAD failure [13, 14]. Furthermore, dressing failure creates an opportunity for skin bacteria to contaminate the catheter insertion site leading to CLABSI or local infection, with a threefold increased risk of CLABSI as a result of skin colonisation and the migration of organisms down the catheter following disruption of the second dressing [15].

Mastisol liquid adhesive (MLA) (Eloquest Healthcare, Inc., Ferndale, MI) is a non-water-soluble gum mastic liquid adhesive designed to improve dressing adherence and integrity [12] and consequently decrease dressing failure. MLA is applied to the skin under the dressing after skin antisepsis. The purpose of MLA is to reduce frequent and often painful dressing changes and the resulting incidence of both CLABSI and MARSI [12], by improving dressing adhesion. A recent study in healthy volunteers found no statistical difference in bacterial growth with the use of MLA compared to standard care alone, supporting its safe use in this patient population [12]. Furthermore, a recent audit of IJ CVADs dressings in a cardiovascular ICU found an improvement with dressing adhesion from 11% (*n* = 4) to 100% (*n* = 30) with the use of MLA [16]. However, despite being in clinical use in Australia for many years, MLA has not been tested rigorously in a randomised controlled trial (RCT). To determine if MLA is a clinical and cost-effective intervention to improve IJ CVAD dressing adherence, we propose a multi-centre, two-arm, parallel group RCT.

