#### Adverse event reporting and harms

Enrolled patients will be monitored and treated for untoward medical occurrences in line with standard clinical care. Therefore, only adverse events which the treating clinicians believe are associated with the intervention will be reported.

In this trial, the following will be considered as serious adverse events (SAEs):DeathCLABSIMARSI

All SAEs from randomisation to 48 h after removal of the CVAD will be recorded on REDCap and reported to the coordinating centre within 24 h.

The minimum information to report will include:Patient study numberNature of the eventCommencement and cessation of eventThe principal investigator’s assessment of the relationship between the study intervention and the event (not related, possibly related, probably related)Whether treatment was required for the event and what treatment was administered

It is the responsibility of each site’s principal investigator to inform the chief investigator and project manager of all SAEs which occur at their site. Copies of reports and correspondence to and from the reviewing HREC and research governance will also be sent to the coordinating centre. The project manager will be responsible for reporting all SAEs to the reviewing HREC and alerting other participating sites of the SAE if required.

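### The SAE outcome counts MARSI with no seriousness condition, so as worded it can consist largely of non-serious skin reactions assessed unblinded

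*Protocol article*

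**What the plan says.** SAEs are defined twice in the protocol article, and the two places agree. Secondary outcomes lists "Serious adverse events (i.e. mortality, CLABSI, MARSI"). Adverse event reporting and harms states "In this trial, the following will be considered as serious adverse events (SAEs):DeathCLABSIMARSI". Both are closed lists, and neither attaches a grade, a need for treatment or any other seriousness condition to MARSI.

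The item after SAEs in the secondary outcomes is a separate one: "Adverse skin events relating to MARSI (e.g. pain, itch, erythema, skin stripping, blister, skin tear, irritant contact dermatitis, maceration, folliculitis or infection"). Background and rationale is similarly broad: "CVAD-related MARSI typically includes bruising, local site infections, pressure injuries, maceration, dermatitis, and mechanical injuries such as skin tears and blisters". The daily check in Table 1 collects "Signs and symptoms of skin injury/reaction • Pain, itch, redness, rash, papules, stripping, blister, etc".

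On reporting, the harms section says that "only adverse events which the treating clinicians believe are associated with the intervention will be reported", and then that "All SAEs from randomisation to 48 h after removal of the CVAD will be recorded on REDCap and reported to the coordinating centre within 24" hours. On assessment, Who will be blinded says that "blinding of patients/clinicians and research staff to the intervention is not possible".

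**The concern.** An SAE outcome is read as a measure of serious harm. Here one of its three components is named without a threshold, and the article's own descriptions of that component reach down to redness and itch. MARSI is also the component most likely to move in this trial. The intervention is a skin adhesive, and its rationale is that fewer dressing changes mean less skin injury, so MARSI could rise or fall with treatment. It is judged by staff who know the allocation, whereas infection outcomes are apportioned by a blinded consultant.

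A difference between arms in SAEs could therefore reflect non-serious skin findings and be reported as a difference in serious harm, in either direction. Sites could also classify the same reaction differently, because nothing tells them when a skin event becomes a MARSI that is an SAE. Mortality is named as an outcome only inside this SAE item.

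**Working it through.** **Reading the definitions together.**
- Both SAE lists name MARSI without qualification.
- The skin event item and the background describe MARSI or MARSI-related events as running from itch, pain, erythema, bruising and dermatitis up to blisters, skin tears and infection.
- Table 1 records signs, and the extent of redness, rash or maceration, but links no level of either to SAE status.
- In the harms section, relatedness and whether treatment was required are contents of an SAE report. They are not conditions for being an SAE.
- The limit to events believed to be associated with the intervention is a causality rule, not a severity rule, and unblinded clinicians apply it.

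No sentence in the article removes a non-serious MARSI from the SAE outcome.

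**Plan's own figures.** The article gives no rate for death, CLABSI or MARSI, so there is no SAE figure to reproduce. Its one sample size does reproduce: for 50% v 25%, two-sided 0.05 and 90% power, n = [1.960·√(2·0.375·0.625) + 1.282·√(0.25 + 0.1875)]² / 0.25² = 76.7, that is 77 per group. This point does not affect it.

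**Illustration with assumed rates.** Let d be death, c CLABSI and m MARSI, with d and c not overlapping and m independent of both.
- P(any SAE) = 1 − (1 − d − c)(1 − m)
- Share of SAE patients qualifying through MARSI alone = [P(any SAE) − (d + c)] / P(any SAE)

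With d = 5%, c = 1%, m = 20%: P = 1 − 0.94 × 0.80 = 24.8%, against 6% without MARSI. The share through MARSI alone is 0.188 / 0.248 = 76%.

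Range, with c = 1%:

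| Death | MARSI | Any SAE | Without MARSI | MARSI alone, share |
|---|---|---|---|---|
| 2% | 5% | 7.9% | 3% | 62% |
| 2% | 30% | 32.1% | 3% | 91% |
| 10% | 5% | 15.5% | 11% | 29% |
| 10% | 30% | 37.7% | 11% | 71% |

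**How much of that is non-serious.** If a fraction f of MARSI is non-serious, the base-case share qualifying only through a non-serious MARSI is 0.188f / 0.248. This is 76% at f = 1 and 38% at f = 0.5. It passes one half when f exceeds 0.124 / 0.188 = 0.66.

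**Between arms.** With d = 5% and c = 1% in both arms, MARSI of 10% v 20% gives any-SAE rates of 1 − 0.94 × 0.90 = 15.4% v 24.8%, with no difference in death or CLABSI.

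**The case against.** The case on the other side is substantial.

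- **No pooled SAE test is stated.** The word composite is used only for CVAD failure, and the statistical methods do not mention a single SAE rate. This stands. The rates above describe what a pooled count would contain, not a planned test.
- **The components are visible elsewhere.** CLABSI is a separate outcome with its own incidence rates, intervals and Poisson regression. Skin events are a separate outcome. Survival status and date of death are collected at 48 h after removal, and each SAE report records the nature of the event. This stands too. A reader might infer that a difference in death or CLABSI would be hidden, or that the trial cannot reach a sound conclusion on serious harm. The article does not support either inference.
- **That every itch scores as an SAE is an inference.** The article lists MARSI and skin events relating to MARSI as two items, and Table 1 at removal lists MARSI apart from signs and symptoms. A narrower, diagnosed MARSI may be meant. That is possible, but the article states no rule drawing the line, and a narrower MARSI would still carry no seriousness condition.
- **MARSI is not always mild.** The background includes pressure injuries and skin tears, and says that MARSI can disfigure or lead to CVAD failure. This stands, and is why f appears in the calculation.
- **The label secures rapid reporting.** That is sensible for a skin product with little prior evidence and no data monitoring committee. But rapid reporting can be kept without scoring every MARSI as serious in an outcome.
- **An article may leave grading to the full protocol.** It may, but here the definition is stated, twice, as a closed list. The problem is what it says, not what it omits.

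**Conclusion.** The point holds as one about classification. Both SAE definitions admit MARSI with no seriousness condition, in an unblinded trial whose intervention acts on the skin, and nothing separates an SAE-level MARSI from an adverse skin event. Under the base assumptions about three quarters of SAE patients qualify through MARSI alone, and between 29% and 91% over the range shown. These figures rest entirely on assumed rates and independence. They equal the non-serious share only if all MARSI is non-serious.

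The damage is confined to the SAE outcome as worded and to how it would be read. The components can be recovered from data the trial already collects, and the primary outcome, its analysis and the sample size are unaffected. The change should be made because it is cheap and because mortality has no outcome of its own outside this item.

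**What to change.** In both places that define SAEs, count MARSI in the SAE outcome only when the event meets a standard seriousness criterion (for example, it is life-threatening, prolongs stay, or needs intervention to prevent lasting damage). Leave all other MARSI in the adverse skin event outcome. Report death, CLABSI and serious MARSI separately by arm rather than as one SAE rate.

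Keep reporting of all MARSI to the coordinating centre within 24 h, as an event of special interest. The criteria for discontinuing or modifying the allocated intervention are not part of this change and stay as written.

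The cost is a wording change and one seriousness item on the SAE form, which already records nature, timing and treatment of each event. MARSI events already reported as SAEs would need reclassifying from those records, preferably without sight of allocation. The SAE count will fall: under the base assumptions, from 24.8% to 15.4% if half of MARSI is serious (1 − 0.94 × 0.90), or to 6% if none is.
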